#### Blinding

Because of the nature of the intervention, it is impossible to mask study participants and the interventionist. However, the study assessors will be masked to the group allocation. To prevent accidental disclosure by study participants, the research assistant will provide a 5-min orientation for each participant just before each data collection period. To ensure the blinding of the assessors, three data collectors who are academic staff at the University of Gondar will be recruited for each assessment time (T1, T2, and T3). One data collector will be assigned for each phase and will not have contact with the study data and participants.

### Intervention arms of the study

The study will have two arms: the treatment group will receive the DSM coaching program, and the control group will continue receiving the usual care (see Fig. 1).

**Fig 1 Fig1:**
[figure not shown]
Study participant flow diagram based on the CONSORT guideline [29]. Key: *T1*, *T2*, *T3* represent time of assessment, *n* number

*Treatment group:* The treatment group will attend a 12-week DSM coaching program culturally adapted from the I-change model [27], an evidence-based health coaching intervention [20]. The DSM coaching program will have six interactive group sessions, including an overview of diabetes, goal setting, dietary management, exercise, blood glucose monitoring and medication, and foot care. In addition, the DSM coaching will also include four individual home-based coaching sessions. Furthermore, a family member who is a direct care provider will have a 10-min orientation after every individual home-based coaching session with the participants.

The principal investigator, who has completed a coaching and counseling course at Queen’s University, Kingston, Canada, will facilitate the DSM coaching sessions. The coach will deliver six 2-h group coaching sessions every 2 weeks for 3 months. The coach will use interactive discussions, experience sharing, demonstration, and home-take assignments to address the program goals. The intervention group will also continue receiving the usual care in the clinic (see Additional file 1: the DSM coaching program).

#### Control group

The control group will continue receiving the usual care in the chronic disease clinic. The usual care is biweekly or monthly clinical appointments, depending on the severity of the illness. Services provided during these clinical visits include history taking, physical examination, laboratory investigation, and medication refills. The available treatments for type 2 diabetes may include oral hypoglycemic agents such as metformin, glipizide, and nateglinide, and injectable insulin. Depending on the severity of the illness and the blood glucose level, doctors may prescribe an oral hypoglycemic agent, insulin, or a combination of both.

### Outcome measures

#### Primary outcomes

##### Feasibility outcomes

The current study will address the eligibility rate, recruitment rate, retention rates, adherence rate, and the acceptability of the DSM coaching program. The progression criteria will determine the success of the DSM coaching program (Table 1).

**Table 1 Tab1:** Progression criteria for the feasibility of the DSM coaching program

**Feasibility outcomes**	**Operational definitions**	**Progression criteria/success**	**Source of data**
Eligibility rate	It is the proportion of people who fulfill the screening criteria.	$$\ge$$ 50% will be acceptable for the future trial	Screening records
Recruitment capacity (rate)	It is the proportion of eligible individuals willing to give consent and randomized to the study in 2-month period.	$$\ge$$ 80% (32+) recruitment rate.	Record review
Intervention adherence	An intervention adherence is the participant’s compliance with attending all group sessions, and all home-based coaching sessions.	$$\ge$$ 80% adherence rate	Session attendances of individual and group sessions.
Retention	The ability of the program to retain participants in the study. The proportion of study participants who completed the study and evaluated at the end of the intervention T2 and end of follow-up T3.	$$\ge$$ 80% retention rate	Record review
Acceptability	It is the perception of study participants that a given intervention is agreeable, palatable, or satisfactory.	$$\ge$$ 75% TAAS score	TAAS survey
Coaching session fidelity	It is the proportion of individual coaching sessions rated as moderate or high.	$$\ge$$ 80% will be an acceptable level of fidelity.	Coaching sessions fidelity checklist rated by an OT
DSM coaching Program fidelity	The proportion of fidelity assessment for the DSM coaching program	$$\ge$$ 80% will be an acceptable level of fidelity.	DSM coaching program fidelity assessment checklist

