##### Study setting

The study will be conducted in the primary care settings of Gondar City, Amhara region, Ethiopia. Gondar City is about 740 km away from Addis Ababa, the capital of Ethiopia [30]. Christianity is the dominant religion, followed by Islam. The most common staple diet in Ethiopia is Injera, made up of teff flour after a consecutive date of fermentation. Almost all Ethiopians eat Injera with a stew of lentils or meat at least once daily [31]. People consume organic food items due to limited access to processed food items. Fasting is a common practice during Lent and Ramadan,hence, the study period will exclude these seasons. Gondar City has one referral hospital, nine primary care centers, and additional private health facilities.

According to unpublished Gondar City Health District reports, more than 10,000 individuals attend regular diabetes clinics in Gondar City health facilities. Individuals with diabetes received diabetes care at the referral hospital, private clinics, and primary care health centers. The hospital serves more than 2600 diabetes patients in the chronic disease clinic, and around 1312 patients have type 2 diabetes [32]. The hospital is a point of referral for newly diagnosed individuals with diabetes from health centers, individuals with complicated diabetes, and individuals with uncontrolled diabetes. Because of the absence of a district or a zonal hospital in the city, the city’s health system is inconsistent with the national referral system. As a result, the hospital provides primary, secondary, and tertiary care for individuals with diabetes. Most individuals with uncontrolled diabetes bypass the health centers and get care at the hospital. In addition, health centers also refer uncontrolled diabetes cases to the hospital. As a result, the study subjects will be recruited from the hospital. The research assistant will take informed consent from volunteers with type 2 diabetes who fulfill the screening criteria. Once the recruitment and baseline assessment are completed, the intervention will be administered in the selected health centers.

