#### Sample size determination

A formal sample size calculation will not be applied for a feasibility RCT study [34]. Hertzog [35] suggests that a sample size of 10–40 participants per group is enough for feasibility studies (Hertzog, [35]. Hence, considering the study’s pilot nature, the intervention’s high intensity, and the limited research fund, we will recruit 40 participants. Twenty participants will be allocated to each arm of the study with a 1:1 ratio.

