### Participant recruitment procedure

A 3-min audio record that briefly explains the purpose of the study and the recruitment process will be prepared in Amharic and played in the waiting area of the chronic disease clinic during working hours. In addition, a 1.5 m × 2 m poster describing the study objectives and the recruitment process will be prepared in Amharic and displayed in the waiting area. Nurses in the chronic disease clinic will receive a half-day training about the study, the screening material, and how to connect eligible individuals with the research assistant. Nurses working in the clinic will screen all individuals with type 2 diabetes and connect them with the research assistant. The research assistant will meet eligible individuals in a separate office in the clinic to discuss the study participation, information sheet, and informed consent.

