##### Recruitment rate

The recruitment rate is the proportion of people enrolled (randomized) in the program. It will be computed as Recruitment rate = (NR/NE) × 100, where NR is the number of randomized participants, and NE is the number of eligible participants.

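### The recruitment progression criterion prints two non-equivalent thresholds as one: 80% of eligible people, and 32 of the planned 40

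*Protocol article*

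**What the plan says.** Three places in the protocol article bear on this.

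- **Table 1 (Feasibility outcomes), recruitment row.** The operational definition reads "It is the proportion of eligible individuals willing to give consent and randomized to the study in 2-month period". The progression criterion beside it is at least "80% (32+) recruitment rate".
- **Recruitment rate section.** The formula agrees with the Table 1 definition on the denominator: "Recruitment rate = (NR/NE) × 100, where NR is the number of randomized participants, and NE is the number of eligible participants".
- **Sample size determination.** The target is fixed: "we will recruit 40 participants", split 20 and 20. The Randomization section prepares 40 envelopes, so 40 is also the ceiling on NR.

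NE is not set in advance. It comes out of screening, which Participant recruitment procedure describes as follows: "Nurses working in the clinic will screen all individuals with type 2 diabetes". The Study setting section puts the hospital's pool at "around 1312 patients have type 2 diabetes". The article does not say whether screening stops when the 40th place is filled. It also does not say whether the 80% or the 32 governs, or whether both are required.

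**The concern.** The count in brackets is presented as the same threshold as the percentage, but it is not a percentage of the quantity that the row defines. One figure measures how many of the eligible people join. The other measures how far the trial gets towards its enrolment target. Those are different feasibility questions, and the row label, which names both a capacity and a rate, merges them.

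Recruitment is a primary feasibility outcome, and the protocol uses the progression criteria to judge the program a success or not. If two readings are available and can give opposite answers, the choice between them could be made once NR and NE are known. That is what a pre-specified criterion is meant to prevent. A trial that fills its places could be reported as missing the criterion, and one with weak uptake that reaches 32 people could be reported as meeting it.

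**Working it through.** **Reproducing the bracketed figure.** The planned sample is 40 (Sample size determination) and the threshold is 80% (Table 1). 0.80 × 40 = 32 exactly. No other quantity in the protocol gives 32, so the count is taken to be 80% of the target. The protocol does not say this in words; it is an inference from the arithmetic.

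**When the two rules are the same.** The percentage rule passes if NR ≥ 0.80 × NE. The count rule passes if NR ≥ 32. The thresholds are equal when 0.80 × NE = 32, that is NE = 40. In whole people NE = 39 also gives the same rule, because 0.80 × 39 = 31.2 means at least 32. At NE = 38 the percentage rule needs 31 (0.80 × 38 = 30.4). At NE = 41 it needs 33 (0.80 × 41 = 32.8).

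**When they differ.** The NR and NE values below are illustrative; the protocol gives none.

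| NR | NE | NR/NE | 80% rule | 32+ rule |
|---|---|---|---|---|
| 32 | 40 | 80.0% | met | met |
| 40 | 50 | 80.0% | met | met |
| 40 | 51 | 78.4% | missed | met |
| 40 | 60 | 66.7% | missed | met |
| 32 | 64 | 50.0% | missed | met |
| 31 | 38 | 81.6% | met | missed |
| 28 | 30 | 93.3% | met | missed |

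The largest NE that still meets 80% is NR/0.80: 40 when NR = 32, 45 when NR = 36, and 50 when NR = 40.

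**The effect of the cap.** Since NR ≤ 40, NR/NE ≤ 40/NE, which is below 0.80 once NE > 40/0.80 = 50. What that means depends on how NE is counted:

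- *Eligible people counted beyond those approached.* Suppose 80 are found eligible, 40 are approached before the places run out, and all 40 accept. Uptake among those approached is 40/40 = 100%, but NR/NE is 40/80 = 50.0%.
- *Counting stops at the 40th randomisation and everyone eligible is approached.* If all accept, NE = 40 and NR/NE = 100%. If 20 decline on the way, NE = 60 and NR/NE = 66.7%, which is a correct reading of uptake.

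The article does not say which of these applies.

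**The case against.** The strongest reply is that the definition and the formula agree with each other, so the formula governs and the 32 is a stray annotation. The described flow is also sequential: nurses pass eligible people to the research assistant, who meets them, and only 40 envelopes exist. If recruitment simply closes at 40, NE above 50 means that more than 20% of eligible people were not randomised, and a result below 80% is the right answer.

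Much of this stands. A reader might infer that a trial in which everyone approached agrees is bound to fail once eligible patients are plentiful. The documents do not support that as a certainty. It requires eligible people to be counted after the places are filled, or without being approached, and the protocol leaves this open. A reader might also be tempted to project the number eligible from the hospital's type 2 patient count and the prevalence figures in the Introduction. Those rates come from other populations. The projection would also ignore most of the eligibility criteria and assume that the whole pool is screened in the 2-month window. No such estimate is used here.

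The reply does not remove the inconsistency itself. Even in a strictly sequential flow, 40 of 60 misses one printed threshold and meets the other. Reading the row as requiring both would end the pass-and-fail conflict, but the text states no joint rule, and the brackets present 32 as the count form of 80%. Nor is this a detail left to a fuller document: the article itself prints a definition, a formula and a threshold that do not agree.

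**Conclusion.** The criterion is wrong as written: its percentage is a share of eligible people, and its count is a share of the planned 40. The two are non-equivalent rather than incompatible. A reader might take them to be mutually exclusive, but both are met whenever at least 32 are randomised and NE is no more than NR/0.80 (for example 40 randomised with up to 50 eligible). Away from NE = 39 or 40 there are possible results on which they disagree, in either direction.

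The conclusion rests on one inference, that 32 is 80% of 40, and the arithmetic for that is exact. The further problem, that the formula falls below 80% beyond 50 eligible people whatever the uptake, is conditional on how NE is counted.

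The consequence is confined to the feasibility judgement. Recruitment is one of seven rows in Table 1, and neither the treatment comparison nor the randomisation is affected. It should still be settled before NR and NE are known.

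**What to change.** Replace the recruitment row of Table 1 with two named criteria, and state how they combine (for example, whether both must be met):

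- **Recruitment capacity:** at least 32 of the planned 40 randomised within 2 months.
- **Uptake:** number randomised divided by the number of eligible people approached while places remain open, with the 80% threshold applied to this.

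Change the formula under Recruitment rate to match. Give the new denominator its own symbol. NE should keep its meaning in the eligibility rate, where all eligible people among those screened are counted, and NA is already used in both the retention and the adherence formulas.

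Deleting the bracketed 32 would remove the direct contradiction, but it would leave open who counts towards NE and would drop the enrolment target from the progression criteria.

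The cost is one table row, one formula and a running count of eligible people approached. The research assistant already meets these people, so the extra work is small.

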##### Eligibility rate

The eligibility rate is the proportion of individuals who fulfill inclusion criteria among those screened. It will be calculated as Eligibility rate = (NE/NS) × 100, where NE is the number of eligible participants, and NS is the number of participants screened.

##### Recruitment rate

The recruitment rate is the proportion of people enrolled (randomized) in the program. It will be computed as Recruitment rate = (NR/NE) × 100, where NR is the number of randomized participants, and NE is the number of eligible participants.

##### Retention rate

The retention rate is the proportion of participants who complete the intervention. The retention rates can be computed as Retention rate = (NA/NR) × 100, where NA is the number of participants assessed at T3, and NR is the number of randomized participants.

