### Study participant retention

Retaining adequate study participants is challenging for many interventional studies involving human subjects. Studies suggest different strategies to increase the retention rate [51, 52]. One of the strategies to retain participants in this study is building effective relationships and treating participants respectfully and compassionately. Hence, the research assistants and data collectors will demonstrate respect and compassion for the study participants. A close follow-up throughout the study period will be the other mechanism to ensure participant retention. The research assistant will closely follow participants through regular attendance and make reminder calls before each session. The research assistant, principal investigator, and participants will discuss and arrange meeting schedules for the group coaching and individual home-based coaching sessions. Participant transport costs will be covered to encourage their participation. In addition, with tangible evidence, any cost incurred by the participant for the purpose of the study will be refunded. The group session will be designed to create active participation through discussion, role play, and demonstration, which will make the sessions attractive and enhance participation.

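### The 80% retention criterion is one pooled ratio over both arms, so it cannot detect differential loss, while the protocol's most specific retention procedures follow sessions that only the coached arm has

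*Protocol article*

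**What the plan says.** Under Sample size determination the protocol states that "we will recruit 40 participants" and that "Twenty participants will be allocated to each arm of the study with a 1:1 ratio".

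The Retention rate section gives a single formula, NA/NR × 100, in which "NA is the number of participants assessed at T3, and NR is the number of randomized participants". The Recruitment rate section uses the same symbol for everyone randomised: "NR is the number of randomized participants, and NE is the number of eligible participants". Table 1 (Feasibility outcomes) describes retention as "The proportion of study participants who completed the study and evaluated at the end of the intervention T2 and end of follow-up T3" and sets the progression criterion at ≥ "80% retention rate". Neither place states a criterion or a calculation by arm.

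Under Study participant retention, the general promise of close follow-up is put into practice as follows: "The research assistant will closely follow participants through regular attendance and make reminder calls before each session". The same section adds joint scheduling of the group and home coaching sessions. Under Intervention arms of the study, the treatment group has six group and four home-based sessions, and the control group has usual care only.

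**The concern.** Retention is one of the primary feasibility outcomes and has a progression threshold. The Discussion says the results will be used to design a definitive RCT. For that two-arm trial, a central question is whether people on usual care alone come back for outcome assessment. A pooled percentage can hide the answer, because good retention in one arm can offset poor retention in the other.

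The conduct of the trial makes uneven loss plausible. Tracking, calls and scheduling are tied to the coaching sessions, so as written they give the coached arm ten planned occasions for contact in 12 weeks. For controls, Table 2 lists two assessments after baseline, at weeks 13 and 24. A pooled pass could therefore carry forward a design in which one arm is poorly followed. In this trial, more of the T2 and T3 questionnaire data in that arm would be supplied by multiple imputation.

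**Working it through.** **Inputs from the protocol.** 40 randomised, 20 per arm (Sample size determination); threshold ≥ 80% (Table 1); one ratio over all randomised (Retention rate).

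**Threshold as a count.** 0.80 × 40 = 32. Table 1 prints the same count, 32+, in its recruitment row; the retention row gives only the percentage. Allowed losses: 40 − 32 = 8.

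**Splits that just pass.**

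| Coached | Control | Pooled | Control lost |
|---|---|---|---|
| 20/20 | 12/20 | 32/40 = 80% | 8/20 = 40% |
| 19/20 | 13/20 | 80% | 7/20 = 35% |
| 18/20 | 14/20 | 80% | 6/20 = 30% |
| 16/20 | 16/20 | 80% | 4/20 = 20% |

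The table can be read with the arms exchanged. These splits need no assumption about true retention. If only 32 were randomised (assumed 16 per arm), 0.80 × 32 = 25.6, so 26 are needed and the largest one-arm loss is 6/16 = 37.5%.

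**How often a pass would hide a low control arm.** The protocol gives no expected retention, so the true rates below are assumptions. Let X ~ Bin(20, p coached) and Y ~ Bin(20, p control), independent. The columns are P(X + Y ≥ 32), P(X + Y ≥ 32 and Y < 16), and, for comparison, a hard gate in each arm, P(X ≥ 16) × P(Y ≥ 16).

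| True retention, coached/control | Pooled pass | Pooled pass with control below 16/20 | Hard gate in each arm |
|---|---|---|---|
| 100% / 65% | 0.76 | 0.64 | 0.12 |
| 95% / 65% | 0.60 | 0.48 | 0.12 |
| 95% / 75% | 0.87 | 0.46 | 0.41 |
| 90% / 85% | 0.945 | 0.13 | 0.79 |
| 90% / 90% | 0.985 | 0.03 | 0.92 |
| 85% / 85% | 0.87 | 0.09 | 0.69 |
| 80% / 80% | 0.59 | 0.10 | 0.40 |

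If the coached arm were the one losing people, the same figures would apply with the arms exchanged.

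**Which retention measures reach which arm.**
- Tied to coaching sessions: attendance tracking, reminder calls, scheduling, and the design of group sessions to be engaging.
- Not tied to an arm: respectful treatment, transport costs, refund of study-related costs, and the 5-minute orientation before each data collection. Both arms also keep their usual-care clinic visits.

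**The case against.** A reader might infer that differential loss is built into the conduct and will run against the controls. The protocol does not support that. Several retention measures apply to both arms, and controls stay in biweekly or monthly care at the clinic. The coached arm also carries six 2-hour group sessions and four home sessions, a burden that could push loss the other way. Only the asymmetry in tracking, calls and scheduling is documented.

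A reader might also infer that the between-arm comparisons would rest on imputed control data. That goes too far. Even in the extreme split 60% of controls are observed, and HbA1c and blood pressure come from chart review, so a missed interview need not lose them.

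On pooling, the wording is not wholly uniform. The Retention rate section opens with "The retention rate is the proportion of participants who complete the intervention", which can describe only the coached arm, and then speaks of rates in the plural, so a by-arm calculation is not ruled out. However, the formula's denominator is everyone randomised, and no by-arm criterion appears. Fig. 1, a participant flow diagram that is not shown here, may give counts by arm, but a display would not alter the pass rule.

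A condensed article may also leave reminders for assessment visits to the full protocol, so their absence here is not an error in itself. The recommendation to add them rests on the session-based procedures that the article does describe.

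The strongest objection is to a hard gate in each arm. With 20 per arm one person is 5 percentage points, and at a true 85% in both arms the chance of passing would fall from 0.87 to 0.69 with no differential loss at all. That objection stands, and the fix does not impose such a gate.

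**Conclusion.** The point holds as a limitation of the progression rule. As written, 32 of 40 is a pass however the eight losses are divided, including 40% loss in one arm and none in the other. That ceiling assumes 40 randomised and full retention in the other arm. The session-based procedures create a risk of uneven loss, of unknown size and in either direction, and the pooled rule cannot detect it.

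The probabilities depend on assumed retention rates. Masking is substantial when the arms differ by 20 points or more (0.46 at 95%/75%, 0.48 at 95%/65%) and small when both are well retained (0.03 at 90%/90%). It is worth correcting because it affects what the trial can say about the feasibility of a two-arm definitive trial, and the correction costs little.

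**What to change.** 1. Keep the pooled criterion of at least 80%. In Table 1 and the Retention rate section, add retention calculated separately by arm at T2 and at T3, with confidence intervals and the between-arm difference. Align the opening sentence of the Retention rate section with its formula and with Table 1, so that retention means being assessed at a named time point in both arms.
2. Require the progression decision to consider the by-arm results. For example, a pooled pass with either arm below 80% (fewer than 16 of 20) would lead to proceeding only with a revised retention plan, rather than to an automatic pass or fail.
3. Under Study participant retention, extend the research assistant's reminder calls and scheduling to the T2 and T3 assessments in both arms.

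**Cost.** Wording changes in three places, and about 40 × 2 = 80 short calls by existing staff. By-arm estimates will be imprecise: 16/20 has an exact (Clopper-Pearson) 95% interval of about 56% to 94%, so they should inform a judgement and not act as a gate. A pass will sometimes be qualified.
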